### Administration of follow-up assessments

The follow-up assessment team is located at a separate University to the baseline/treatment team to maximise blindness and independence. Follow-up assessors are blind to treatment allocation and facilitate completion of follow-up assessments via the Internet to all consenting participants regardless of treatment participation. Follow-up assessment occurs at 26, 39, 52 and 64 weeks post-baseline. There is good evidence that web-based assessments result in reliable and valid ratings of depressive and alcohol use disorders [38].

In line with best practice standards and our previous trial experience, the following strategies are employed to maximise retention in treatment and assessment: (1) obtain multiple contact modes at baseline; (2) rapid and assertive response if contact is temporarily lost (e.g. within 24 h); (3) solicitation of consent to continued assessment when participants wish to cease treatment; (4) negotiation of a reduced set of assessment core measures (i.e. of primary outcomes) when participants are unwilling to undertake the full follow-up protocol; (5) $20 AUD reimbursement for costs and time at baseline and a bonus ($20 AUD) for completing all scheduled follow-ups.

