## Statistical analysis plan

Data on screening, refusals and dropout are coded and reported as per CONSORT guidelines, and primary analyses use intention-to-treat. Preliminary analyses compare treatment groups for any baseline or health service utilisation differences using proportions for categorical variables and means/standard deviations for continuous variables.

The primary outcomes will be compared between groups at each time point using random effects linear regression that includes data from all time points. Separate models will be fitted for each outcome variable. The models will include the fixed effects of treatment (Online Monthly Self-assessment as referent category), time, the interaction between treatment and time as well as the baseline score and baseline score-by-time interaction. The primary contrast will be the difference in least squares means between treatment groups at week 64.

Since the standard errors for the fixed effects in the model depend on the variance-covariance structure that is used in the analysis, we will examine several possible structures including models with random slopes and intercepts, as well as a variety of error structures for the repeated measures (compound symmetry, AR1, Toeplitz). The model with the smallest Akaike Information Criterion (AIC) will be selected as our final model.

The mixed model provides unbiased estimates of the treatment effect under the assumption that data are missing at random (MAR). Since the possibility of non-ignorable missingness cannot be excluded, we will conduct sensitivity analyses using non-ignorable pattern-mixture and selection models to investigate the robustness of our conclusions across these different models for missing data.

Continuous secondary endpoints will be analysed using the model described above, dichotomous secondary endpoints will be modelled using logistic mixed models.

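### The smallest-AIC rule for the primary model's covariance names no structure that can follow a variance change at week 64 alone, so the primary standard error can be too small or too large

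*Protocol article*

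**What the plan says.** The Statistical analysis plan section fits a separate random effects linear regression to each primary outcome, with fixed effects of treatment, time, "the interaction between treatment and time as well as the baseline score and baseline score-by-time interaction". It then states: "The primary contrast will be the difference in least squares means between treatment groups at week 64".

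On covariance it reasons: "Since the standard errors for the fixed effects in the model depend on the variance-covariance structure that is used in the analysis", and continues "we will examine several possible structures including models with random slopes and intercepts". To these candidates it adds "a variety of error structures for the repeated measures (compound symmetry, AR1, Toeplitz"). The rule is "The model with the smallest Akaike Information Criterion (AIC) will be selected as our final model". No unstructured matrix, heterogeneous version of the named structures or robust standard error is mentioned.

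On missing data it says: "The mixed model provides unbiased estimates of the treatment effect under the assumption that data are missing at random (MAR"). It adds pattern-mixture and selection models as sensitivity analyses for non-ignorable missingness.

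The section on administration of follow-up assessments gives the visits: "Follow-up assessment occurs at 26, 39, 52 and 64 weeks post-baseline". The Interventions section gives website access for 12 months from randomisation. The Discussion, under changes since registration, says that the plan printed in the article is the one that will be carried out.

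**The concern.** A contrast at one visit takes its standard error largely from the variance at that visit. Compound symmetry, AR1 and Toeplitz, in standard form, estimate one variance pooled over all visits. Random intercepts and slopes let the variance move, but only along a quadratic in time, so they cannot follow a change confined to the last visit. Week 64 is the only follow-up after access ends, which makes a change in spread or correlation there plausible. If none of the named candidates can fit it, the best AIC among them still carries a wrong week-64 standard error, and both primary tests are affected.

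A second effect comes through dropout. The plan assumes 30% attrition. In a likelihood analysis the covariance model decides how earlier visits inform the missing week-64 values. MAR alone therefore does not give an unbiased estimate; the covariance model must also be adequate. The planned sensitivity analyses address non-ignorable missingness, not this.

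**Working it through.** **Benchmark.** The article gives no visit-specific SDs or correlations, so it has no standard error to reproduce. The benchmark is its 2.5% type 1 error rate. Sidedness is not stated; two-sided is assumed, so z = 2.2414.

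**Inputs from the article.** Four follow-ups, 123 per arm (369 in all), 30% attrition, the fixed effects above, contrast at week 64.

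**Assumptions not in the article.** Correlations 0.65, 0.55 and 0.45 at lags of one, two and three visits unless noted; SDs relative to 1; no true effect; dropout completely at random, mildly MAR, or strongly MAR in opposite directions in two arms. Each named structure is fitted on its own.

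**Formula.** With r = model SE / true SE and d = bias / true SE, actual error = Φ(−zr − d) + Φ(−zr + d). With no bias this is 2[1 − Φ(zr)].

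**Step 1: if a common-variance structure is kept (complete data).** r = √(mean variance / week-64 variance).
- Relative variances 0.8/0.9/1.1/1.2: r = √(1/1.2) = 0.913, error 0.041.
- 0.7/0.9/1.1/1.3: r = √(1/1.3) = 0.877, error 0.049.
- 1.2/1.1/0.9/0.8: r = √(1/0.8) = 1.118, error 0.012.

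**Step 2: let AIC choose for these three trends.** With the assumed lag correlations, random slopes beat Toeplitz by 8, 23 and 9 AIC units, and the error is 0.024, 0.025 and 0.019. With a flat correlation of 0.6, random slopes win again: 0.027, 0.028 and 0.022. With AR1 correlation of 0.7, AIC picks AR1 and the Step 1 figures apply.

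**Step 3: AIC winner among the four named structures, with about 30% dropout by week 64** (large-sample REML fits scaled to 369 participants).

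| SD pattern | AIC winner | r | Actual error |
|---|---|---|---|
| Equal | Toeplitz | 1.00 | 0.025 |
| Rising steadily, 1.0 to 1.3 | Random slopes | 0.99 | 0.027-0.030 |
| Falling steadily, 1.3 to 1.0 | Random slopes | 1.07 | 0.017 |
| 1.3 at week 64 only | Random slopes | 0.93 | 0.038 |
| 1.3 at week 64 only, weaker correlation with week 64 | Random slopes, ahead of Toeplitz by only 1-2 units | 0.87 | 0.052-0.060 |
| 0.75 at week 64 only | Toeplitz and random slopes tie | 1.16-1.25 | 0.005-0.016 |

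Check of row 4: zr = 2.2414 × 0.926 = 2.076, and 2[1 − Φ(2.076)] = 0.038. Check of the upper end of row 5: r = 0.868, d = 0.053/0.1994 = 0.266, so Φ(−2.211) + Φ(−1.680) = 0.0135 + 0.0465 = 0.060. Separate complete-data fits gave 0.036-0.041 for an SD of 1.3 at week 64 alone and 0.009 for 0.75.

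**Step 4: bias of the AIC-chosen structure.** Under strong differential MAR dropout it was about 0.05 SD in row 5 and 0.04-0.07 SD in row 6. Under mild MAR it was about 0.03 SD at most in those two rows. The largest value, 0.069, is 0.069/0.25 = 28% of the 0.25 SD target difference.

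**Step 5: unstructured covariance.** It has 4 × 5 / 2 = 10 parameters. In every scenario r was 0.997-1.000, the error 0.025-0.026 and the bias at most 0.012, about one Monte Carlo standard error. Offered to AIC, it had the smallest value in every unequal-variance scenario. With equal variances it was 12 units worse than Toeplitz, which does no harm there.

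**The case against.** The best defence is that random slopes are the first candidate the plan names, and AIC usually finds them when variances trend. This stands. A reader might take the 4.1%, 4.9% and 1.2% of Step 1 as the plan's error rates, but those need AIC to keep a common-variance structure, as under AR1-type correlation.

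The plan's wording also leaves the list open, so unstructured is not ruled out, and a fuller document might name it. That is fair, and Step 5 shows that adding it to the list would remove most of the problem. But the article names its candidates and a rule, and says this is the plan to be carried out. Pointing to a better choice does not ask for detail that an article normally omits.

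Third, the rule is fixed in advance and AIC does not look at the treatment p-value. A reader might infer that data-driven selection itself inflates the error. No such inflation is shown, and with equal variances the error is 0.025.

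Finally, ten parameters presumes four visits. The model uses data from all time points, and Table 1 also schedules the DASS21 and alcohol diary at the self-assessments. The Secondary endpoint section assigns those to the rate of change, so four is the natural reading, though not an explicit one.

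**Conclusion.** The point holds in a limited form. The named candidates cannot represent a change in variance or correlation confined to week 64, and the primary contrast is at that visit. In that case the AIC-chosen test runs at about 3.6-6% (week-64 SD 30% higher) or about 0.5-1.6% (25% lower) instead of 2.5%. Trending variances with AR1-type correlation can do similar harm. With equal variances there is none, and with steady trends where random slopes are chosen the error is about 1.7-3.0%.

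The sizes rest on assumed SDs, correlations and dropout. The article gives no evidence that a week-64 shift will occur, only a design that makes it plausible. Two stronger inferences are not supported. One is that the standard error is wrong in a known direction: it can go either way, and nothing in the article says which. The other is that the dropout correction is seriously biased: the bias is at most about 0.07 SD and appears mainly under strong dropout in opposite directions. The MAR sentence is incomplete rather than badly misleading. This is worth correcting before analysis, but it does not undermine the design.

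**What to change.** Pre-specify, for both primary outcomes, a model for the four follow-ups (26, 39, 52 and 64 weeks) with categorical time, unstructured covariance, REML and Kenward-Roger degrees of freedom. State the fallback order if it does not converge: heterogeneous Toeplitz, then heterogeneous AR1, each with robust standard errors. Say explicitly that the monthly self-assessments do not enter this model, since the count of 10 parameters depends on that.

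If the team prefers to keep AIC, the minimum change is to add unstructured and heterogeneous-variance structures to the list and to close it.

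Amend the missing-data sentence to say that validity under MAR also requires a correctly specified model, including its covariance.

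The cost is a change of wording, and a negligible loss of degrees of freedom if a simpler structure is true.

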### Sample size and power calculations

Our previous trials indicate approximately 25 % attrition over a 52-week follow-up period [40]. Recruiting 123 participants per group (369 participants across 3 experimental groups) and assuming an attrition rate of 30 %, we anticipate having complete data from 87 participants per group at 64 weeks (*n* = 261).

Our projected sample size at 64 weeks provides sufficient statistical power (at the standard level of 0.80) to detect differences between treatment groups of 0.25 standard deviations or greater, with a type 1 error rate of 2.5 %. Using baseline data from our previous studies with the target population and the DEAL resource [41], this corresponds to a difference between conditions of 1.3 drinks/day, or 9.4/week, and of 2.4 on the DASS21. These differences are towards the lower limits of clinical significance. However, within-condition changes are likely to be substantial. Consistent with our previous research, differences between treatment groups of <0.25SD, provided there are equivalent retention rates and therapeutic alliance ratings, will not be considered clinically significant.

## Discussion

The iTreAD project focuses on a common clinical problem that causes substantial functional, economic, and health impacts; comorbid depression and binge drinking. These conditions are currently under-treated, contribute significantly to the global disease burden and are at their peak in young adulthood. Offering treatments of low cost and with wide reach to affected people will address current inequities of treatment access for these problems, and provide a youth-appropriate modality of treatment delivery. These results will have profound implications for service design and health policy, and speak to important questions about the nature of treatment effects in general.

In commencing the iTreAD study and engaging our study population, two key learnings have emerged, resulting in changes to the study design and delivery to better suit the needs of young people wanting to access treatment (via our study) for depression and binge drinking concerns.Participant preferences for contactOur previous trials that have integrated Internet and computerised interventions into the clinical treatment of comorbid depression and addictive disorders, suggested that real time therapist-support was an influential factor in a potential participant’s decision to enrol in the study [21, 42]. Regardless of whether the treatment provided was entirely face-to-face with a therapist, or supplemented with a computerised treatment program, participants have previously reflected that more face-to-face support would have increased satisfaction with treatment [43]. Accordingly, the iTreAD methodology incorporated several points of “real-time” clinical contact with participants (via phone). For the 18–30 year age group, however, we have found the phone-based contact requirement to be a barrier to participation. For example, we had a significant proportion of participants who were eligible, and completed their online baseline assessment, but could not be contacted via telephone to speak with a clinician to complete their clinical interview, receive their randomisation, and commence the study treatments. Switching to a fully automated online consent and assessment process has seen significantly better retention and participation by the young people engaged in the trial to date, and progression through to randomisation and treatment for those young people who were unable to complete the phone-based ‘real time’ study phases.Duty of care considerations in non face-to-face trialsAn important observation in the target population for the iTreAD study is that, despite setting the threshold for entry at relatively low levels of depression and binge drinking behaviours, study participants tend to be those reporting more severe depressive symptoms and regular (daily) alcohol use. By including additional optional mental health domains in our baseline assessment, we have also detected significant levels of exposure to traumatic events, and high levels of current trauma symptoms. This has presented an ethical and clinical challenge, given the nation-wide recruitment strategy, and the preference for non ‘real time’ contact by participants in our study. It has taken the combination of our expertise across Internet trials and significant clinical expertise in working with people with severe comorbidities to safely engage and support the young people in our trial. The online format for baseline assessment completion, whilst appealing to the age group, has also potentially provided the anonymity that might encourage higher levels of disclosure of traumatic events, severe symptoms, and high-risk behaviours than for traditional assessments. This is an important advantage of the Internet, however it also requires a considered and careful response to participants in managing these disclosures. We have thus devised a careful strategy to respond to these disclosures, which involves a range of ‘real time’ options (phone calls, personalised private messaging), and setting a threshold for self-report of suicidal and traumatic symptoms that automatically triggers a ‘real time’ response. Having clinically trained staff (e.g. clinical psychologists) is essential in these situations, as is regular clinical supervision sessions, and access to ‘real time’ expertise to work through options for follow-up, referral, and engagement of local crisis services to the participant should that be indicated.Changes to the protocol since Clinical Trials RegistrationEligibility Criterion for Depression: We have set eligibility for the current trial at a DASS-Depression scale of 5 or greater to ensure we recruit participants with current levels of depressive symptoms. Our clinical trials registration specifics an eligibility criterion for the DASS of 12 or greater on the full scale. This was modified as the criterion was not specific or sensitive enough to recruit our target sample.Removal of the Structured Clinical Interview for DSM SCID, [44]. With removal of the phone-based assessment, we also had to remove the SCID-Depression and SCID-alcohol scales from our baseline assessment, as these scales are not currently validated for delivery in self-report format. We will present SCID data on all participants who provided this information prior to the implementation of full online baseline assessment.Statistical Analysis Plan: since completion of the clinical trials registry, we have engaged the independent expertise of a designated statistician to develop the statistical analysis plan (and to carry out said plan) for the current trial. The plan reported in this study protocol is the analysis plan that will be undertaken at the conclusion of the study.
